### Blinding

The following guidelines will be used to ensure that the data is blinded during intervention and assessment. The preassessment will precede the randomization and will be conducted by the study assistants on site; these study assistants will not be informed about the study goals in general and the computer training in specific. The assessment of anthropometric data will be conducted by medical staff not involved in the study and therefore blind to hypotheses and study design. The allocation of the participants will be done by fax using a mixed letter coding system. Therefore the study assistants and the participants will be blind to the treatment allocation. Data collection and data analysis will be independently conducted. A scanner is used to for the data entry. Whenever feasible, online questionnaires will be used for the collection of the follow-up data. In any case, only the code of the child will be given, which allows no conclusions about the treatment allocation. The child’s physician will provide the study center with the anthropometric data at the follow-up. The physician will also be blind to the goals of the study. Reimbursement will be used to prevent high as well as selective attrition rates. Regular unblinding will take place after the completion of the data analysis. No intention exists for early unblinding.

### Participant discontinuation and safety

Participating children and adolescents, as well as their parents, can withdraw their study participation at any time. In addition, they can discontinue treatment without giving any reasons. Since no adverse effects of such a training program were reported in the literature (for example, [42]), we do not expect any severe side effect of our treatment approach. We will document any reported negative effect from the participants of the computer training. In addition, the occurrence of disturbed eating patterns will be monitored at the follow-up assessments.

### Intervention evaluation by the participants

At the end of the AAT-training sessions, children and adolescents will fill in a self-constructed acceptance questionnaire including open questions to give the participants the opportunity to comment on their experiences. In addition, the assistants will note signs of discomfort.

### Trainer meetings and monitoring

Trainer meetings are not necessary because we are using a standardized computer training. The study coworkers will be trained on how to approach eligible participants and how to apply the computer training and the assessment sessions in a standardized way. Furthermore, they will be provided with a study manual. Therefore the standardization of recruitment, data collection and intervention assures data quality.

### Ethical approval

This trial received written approval by the ethical committee of the University of Potsdam (proposal 29/2012; vote on 05 November 2012). The study will be conducted according to the principles outlined by the Declaration of Helsinki (version 2013). The staff commits themselves to all pertinent national laws and the ICH guidelines for GCP issued in June 1996 and CPMP/ICH/ 135/95 from July 2002. All relevant parties will be informed in case of important protocol modifications.

### Data

All staff members that come into contact with the data are subject to professional secrecy and data protection conditions. Personalized data will be assessed via questionnaire and will be stored in a locked cabinet separate from the other data and not electronically filed. With respect to the reaction time, data they will be saved on the respective computer on each study site. The recordings will be copied onto a password protected CD by the study nurse and sent by mail to the study office. The access to the computer is restricted; the computer is not connected to the internet. The training sessions start after entry of the code number by the study assistant. All additional data (medical sheets and questionnaires) are marked with code numbers and pseudonymized. Following the final assessment, all personal data will be destroyed to ensure immediate complete anonymization. Before consent is given, all potential study participants receive adequate written information about the aims and implications of the study. Informed consent will be obtained from children and their parents by the study assistants.

All primary outcome data (weight data) will be verified supplementary to the electronic data entry via scanner. Additionally, 20 % of the questionnaire data will be double checked by staff. A Data Monitoring Committee will not be appointed, as risks from the intervention are neither reported nor expected.

### Data analyses

Missing data of the computer-assisted measurements will not be replaced since there are very unlikely and might be a sign of recording problems. With respect to the questionnaire data and the primary outcome, missing values will be replaced by unbiased substitution (EM-algorithm). As a first step, an analysis of whether the children in the intervention group show a learning effect compared to the control will be conducted. This learning effect would be characterized by faster reaction times at the end of the training. Primary and secondary outcomes will be tested performing an ANCOVA from post-intervention to the 12-month follow-up between the two random groups, adjusted for the baseline measurements. They will be analyzed by performing an ITT as well as a per-protocol analysis (PPA) that excludes all drop-outs. The association between self-regulation and sustained weight loss at 12-month follow-up and potential moderators (binge eating; psychosocial strain) will be tested using hierarchical multiple regression analyses. As a second step, the BMI-SDS change will be dichotomized (successful versus not successful) in order to perform logistic regression analyses. Relevant trial results will be published in the corresponding platforms.

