### Sample size and enrolment

So far, there are no studies that have conducted an AAT on nutrition in children. Therefore, a referral upon existing data could not be used in the power calculation. In total, we only expect small differences between the groups for the primary outcome (age- and gender-specific BMI-SDS course after 6 to 12 months following the intervention), because the AAT will only be an additional offer for children and adolescents within the multidisciplinary rehabilitation. Comparable effect sizes are also assumed for food intake and weight-related quality of life. On the other hand, we expect average effect sizes for the employed self-control measures as secondary outcomes because the AAT is a specific training of these skills. The power calculation was performed with the program *g power 3.1* [30] in several steps to take into account these considerations. The power was set to .8 and the alpha error to .05. For a small effect (f = .2), 199 subjects are needed, with 99/ 100 per group for an analysis of covariance (ANCOVA) that includes three covariates (age, gender, and educational background). Because the data will be primarily analyzed on the basis of an intention-to-treat approach, only a small number out of the 13 patients per group were taken into consideration (see [22]). A subsequent post-hoc compromise analysis (considering differing effect sizes for primary and secondary outcomes) has confirmed that this sample size (n = 226) is sufficient to depict small effects with a power of .9. On that basis the following will occur:n > 600 will be assessed for eligibility,n = 226 will be allocated to trial, andan intention-to-treat approach (ITT) will be conducted on n = 226 (the complete analysis should include n = 199 participants).

To prevent selective drop out and incomplete outcome data, all participants will be reimbursed for completely filling in the questionnaires in the follow-up period and will receive cheerful mail on special occasions (birthday, Easter or Christmas greetings). In addition, the family doctors will receive a monetary incentive for providing anthropometric data (weight and height).

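### EM substitution of missing BMI-SDS followed by an ordinary ANCOVA on 226 children either understates the standard error or dilutes the effect, moderately so at the planned 12% loss

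*Protocol article*

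**What the plan says.** The Data analyses section sets the handling of missing values, for BMI-SDS and the questionnaires alike: "missing values will be replaced by unbiased substitution (EM-algorithm". The test comes next: "Primary and secondary outcomes will be tested performing an ANCOVA from post-intervention to the 12-month follow-up between the two random groups". The model also takes account of each child's starting value. Two analysis sets are named: "They will be analyzed by performing an ITT as well as a per-protocol analysis (PPA) that excludes all drop-outs".

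The Sample size and enrolment section supplies the numbers. It plans that an "intention-to-treat approach (ITT) will be conducted on n = 226 (the complete analysis should include n = 199 participants". It also makes intention-to-treat the leading analysis.

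The article mentions no multiple imputation, pooling of several filled-in data sets, variance correction or direct-likelihood analysis. It does not list the variables in the EM model, so it is open whether arm is one of them.

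**The concern.** Under missing at random, the EM algorithm estimates means and covariances well. The label *unbiased* may hold for those. It does not carry over to an ANCOVA run on a data set whose gaps were filled with EM predictions. A predicted value lies on the fitted surface: it has no residual scatter and hides the error in the fitted surface itself. The ANCOVA nevertheless counts it as one more measured child.

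What goes wrong depends on the open choice:

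- **Arm in the EM model.** The effect estimate is right on average, but its standard error is too small and the test rejects too often.
- **Arm not in the EM model.** Children with missing data in both arms get the same prediction rule, so the difference between arms is pulled towards zero.

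This is the primary test. Follow-up weight and height come from family physicians 6 and 12 months after discharge, and the plan itself allows for loss.

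**Working it through.** **1. The plan's own figures.** Inputs from Sample size and enrolment: f = .2, α = .05, power .80, two groups, three covariates. For the ANCOVA F test, λ = f²N = .04N, with 1 and N − 5 degrees of freedom.

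- N = 198: power .7996. N = 199: power .802. The stated 199 is reproduced.
- 226 − 199 = 27, and 27/226 = 11.9% loss. Conversely 199/.88 = 226.1. The 226 is therefore 199 complete children plus a 12% allowance.

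**2. Approximation.** Let m be the share with a missing outcome, missing completely at random, with no later visit to help the prediction. Let σ be the ANCOVA residual SD and n = 226.

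*Arm in the EM model.* Filled-in values add almost nothing to the residual sum of squares, so the estimated residual variance is about (1 − m)σ².

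- Model SE ≈ 2σ√(1 − m)/√n
- True SE ≈ 2σ/√(n(1 − m))
- Ratio ≈ 1 − m
- Actual type I error ≈ 2Φ(−1.96(1 − m))

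At m = .12: ratio .88, type I error 2Φ(−1.725) = .085. At m = .20 (assumed): ratio .80, type I error 2Φ(−1.568) = .117.

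*Arm not in the EM model.* Only the observed share carries the difference, so the estimate is about (1 − m) times the true effect: .88 at 12% and .80 at 20%. Its true SE shrinks by the same factor, to 2σ√(1 − m)/√n, which equals the model SE. The null test therefore keeps its level, and power is about that of complete cases.

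**3. Simulation.** N = 226, 1:1, ANCOVA of the 12-month value (T4), 1,500 to 2,500 runs per scenario. Assumptions not in the documents: multivariate normal data; T1–T2 correlation .9; T3–T4 correlation .85; baseline–T4 correlation .7 (adjusting for T1) or .85 (adjusting for T2); T4 missing completely at random; 80% of those children also missing T3.

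| Loss at T4 | Arm in: model SE/true SE | Arm in: type I error | Arm out: type I error | Arm out: share of effect kept |
|---|---|---|---|---|
| 12% (plan) | .89–.91 | .07–.09 | about .05 | .90 |
| 20% (assumed) | .83 | .11 | .05 | .83 |

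The step 2 values are slightly worse because some simulated children still have a 6-month value that improves the prediction.

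**4. Other assumptions.**

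- With T1–T4 correlations of .80 to .95 and T3 and T4 always missing together, at 12% loss and with arm in, model SE .0755 against true SE .084 gives a ratio of .90 and type I error .076. With arm out, a true effect of .24 is estimated as .210 (.875 kept); at 20% loss it is .192 (.80 kept).
- When half of the children missing T4 still have T3, the estimate with arm out is .224 (.93 kept). With arm in, type I error is .076, against .091 with T3 always missing.
- Over all runs at 12% loss, type I error with arm in is about .06 to .09, and dilution with arm out is about 7 to 12%. At an assumed 20%, they are about .11 and 12 to 20%.

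**5. Remedy, same simulation as step 3.** Multiple imputation (20 imputations, arm in the model, Rubin's rules) at 12% loss gave type I error .045 to .054, SE ratio 1.00 to 1.02, an effect within about 1% of the truth, and power .81 to .82.

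**The case against.** **The p-value is not wrong in both cases.** A reader might infer that the test and confidence interval fail whichever EM model is used. That does not hold. With arm left out, type I error stays near .05 and power at 12% loss is .80 to .82, about the same as with multiple imputation. In that case the effect estimate is at fault, not the null test.

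**The sample size does not rest on imputation.** A reader might take the sentence that begins "Because the data will be primarily analyzed on the basis of an intention-to-treat approach, only a small number" to mean that substitution is credited with restoring information, and so want the sample size redone. The sentence is awkward, but the section already gives power .80 for 199 children and expects 199 complete. The 226 only adds the loss allowance.

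**Large distortions are not documented.** Type I errors of .15 or .20 appear in simulation only at 30 to 40% loss. The documents support about 12%, and they describe incentives, reminders and contact with physicians to limit loss. Higher rates remain assumptions.

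**The per-protocol analysis gives a second view.** It excludes drop-outs and so comes close to a complete-case ANCOVA, which held its level in simulation. This is true and useful, but it is not the leading analysis and does not correct the intention-to-treat result.

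**The article is condensed.** It does not say that one data set is filled in, or that the values carry no residual noise; both are inferences. Replacement by substitution followed by one ANCOVA on 226 most naturally reads that way. Added residual noise would reduce the standard-error problem without removing it (not simulated). The method itself, and its label as unbiased, are stated, so this is not merely a detail left to a fuller plan.

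**Conclusion.** The concern holds in a bounded form. Read as a single filled-in data set, EM substitution followed by ordinary ANCOVA on 226 miscalibrates the primary intention-to-treat analysis in one of two ways. With arm in the EM model, the standard error is about 10% too small and type I error is about .06 to .09. With arm out, the effect is diluted by about 7 to 12% while the null test stays valid. The two faults are alternatives, and the article does not settle which one applies.

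At the planned 12% loss the size is moderate; it grows as more follow-up weights are missing. The direction follows from the method. The figures rest on assumed correlations, normality, data missing completely at random, and a T4 ANCOVA adjusted for T1 or T2, because the article does not pin down the model's exact form. The sample-size figure stands.

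**What to change.** In the intention-to-treat analysis, replace EM substitution by one of these:

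- **Multiple imputation**, with arm, the T1 to T3 values and the planned covariates in the imputation model, the planned ANCOVA run in each data set, and results pooled by Rubin's rules; or
- **A likelihood-based repeated-measures model** on all observed post-baseline BMI-SDS values, keeping the planned baseline adjustment and the covariates named in the sample size section (age, gender, educational background).

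Treat the questionnaire outcomes the same way, and delete the word *unbiased*. Report observed and missing counts by arm and visit.

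The cost is a change of wording and a standard software routine. No new data are needed, and 199 complete and 226 allocated remain as they are. Confidence intervals will be slightly wider than under EM substitution, because they then reflect the information actually collected.

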**Methods/Design:**

In a multicenter, prospective, parallel group, randomized controlled superiority trial, 226 obese children and adolescents aged 8 to 16 years will be allocated either to a newly developed computer-training program to improve their self-regulation abilities or to a placebo control group. Randomization occurs centrally and blockwise at a 1:1 allocation ratio for each center. This study is performed in pediatric inpatient rehabilitation facilities specialized in the treatment of obesity. Observer-blind assessments of outcome variables take place at four times: at the beginning of the rehabilitation (pre), at the end of the training in the rehabilitation (post), and 6 and 12 months post-rehabilitation intervention. The primary outcome is the course of BMI-SDS over 1 year after the end of the inpatient rehabilitation. Secondary endpoints are the self-regulation skills. In addition, health-related quality of life, and snack intake will be analyzed.

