### Study setting

This study is being conducted in four study centers, all of which are inpatient medical rehabilitation facilities (Bad Kreuznach, Bad Orb, Idar Oberstein, and Sylt). These clinics were chosen because of their specialization in the treatment of childhood obesity and delivering their intervention according to the national guidelines. Participating study centers and investigators are fully listed in the German Clinical Trials Register (DRKS00007879).

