### Randomization procedure and treatment allocation

Randomization and allocation in a ratio of 1:1 for each clinic to treatment aim will occur before the interventions begin. The randomization is computer based [40] and centrally performed. A post-hoc evaluation by descriptive statistical comparisons between the intervention and the control group in relevant sociodemographic data (age, gender, and sociodemographic data) will be conducted to assess the effectiveness of the randomized assignment. The study assistant will receive the fax with the randomization that only discloses the allocation of the patients to either group A or B (allocation concealment).

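### Allocation is blocked within each of four centres, but the stated ANCOVA does not include centre; if centres differ, its standard errors are somewhat too wide

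*Protocol article*

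**What the plan says.** All statements are in the protocol article.

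- **Allocation.** The Methods/Design part of the abstract states: "Randomization occurs centrally and blockwise at a 1:1 allocation ratio for each center". The section Randomization procedure and treatment allocation repeats the ratio by clinic: "Randomization and allocation in a ratio of 1:1 for each clinic".
- **Number of centres.** Study setting: "This study is being conducted in four study centers, all of which are inpatient medical rehabilitation facilities".
- **Analysis model.** Data analyses describes one ANCOVA for primary and secondary outcomes, comparing the arms "between the two random groups, adjusted for the baseline measurements". Neither centre nor any demographic covariate is named there.
- **Sample-size model.** Sample size and enrolment uses an "analysis of covariance (ANCOVA) that includes three covariates (age, gender, and educational background"). Neither baseline BMI-SDS nor centre is named. The inputs are: "The power was set to .8 and the alpha error to .05". The result is: "For a small effect (f = .2), 199 subjects are needed, with 99/ 100 per group".

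**The concern.** Two things do not fit together.

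First, centre is a design factor. Balancing the arms within each centre means that differences between centres largely cancel from the arm contrast, so the estimate is more precise than under unrestricted randomisation. A model with no centre term does not recognise this. It counts the between-centre variation as residual noise and reports a standard error larger than the real sampling error. Intervals come out too wide, the test rejects less often than its nominal level, and some power is given away. A centre effect is plausible because each clinic delivers the multidisciplinary background programme itself. The trial expects only a small effect and is sized at 80% power, so it has little precision to spare.

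Second, the covariates that support the sample size are not those named for the analysis. A reader cannot tell from the article which set the confirmatory test will carry.

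**Working it through.** **Step 1: reproduce the plan's figure.** Inputs from Sample size and enrolment: f = .2, alpha .05, power .8, two groups, three covariates. For the ANCOVA main effect, the noncentral F distribution has 1 and N − 2 − c degrees of freedom and noncentrality f² × N, where c is the number of covariates. With c = 3, N = 198 gives power .7996 and N = 199 gives .8016. The stated 199 is reproduced exactly.

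**Step 2: does the covariate mismatch change N?** In this formula covariates enter only through the degrees of freedom.

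| Covariates | c | Power at N = 199 | Smallest N for .80 |
|---|---|---|---|
| Baseline only | 1 | .8017 | 199 |
| Age, gender, education | 3 | .8016 | 199 |
| Baseline + those three | 4 | .8016 | 199 |
| Those four + three centre indicators | 7 | .8015 | 199 |

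It does not, and adding centre does not raise N either.

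**Step 3: cost of leaving centre out.** Let R be the share of residual variance due to centre. The article gives no value, so 2%, 5% and 10% are assumptions. Set the residual SD including centre to 1, with arms balanced within centre.

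- Ratio of model standard error to true standard error: 1/√(1 − R).
- True type I error without centre: 2 × [1 − Φ(1.96/√(1 − R))].
- Noncentrality on the total scale: f × √N = .2 × √199 = 2.821.
- Power with centre (normal approximation): Φ(2.821/√(1 − R) − 1.96).
- Power without centre: Φ(2.821/√(1 − R) − 1.96/√(1 − R)). The true sampling error is the same small one, but the critical value is effectively inflated.

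Worked for R = 5%: √.95 = .9747. The standard-error ratio is 1.026. Type I error is 2 × [1 − Φ(2.011)] = .044. Power with centre is Φ(2.895 − 1.960) = .825, and without it Φ(2.895 − 2.011) = .812. The difference is .013.

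| Centre share (assumed) | SE too wide by | True type I error | Power without centre | Power with centre | Difference |
|---|---|---|---|---|---|
| 0% | 0 | .050 | .805 | .805 | 0 |
| 2% | 1.0% | .048 | .808 | .813 | .005 |
| 5% | 2.6% | .044 | .812 | .825 | .013 |
| 10% | 5.4% | .039 | .818 | .845 | .027 |

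The normal approximation gives .805 at R = 0, against .802 from the F distribution. The differences between columns are what matter.

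**Step 4: check by simulation.** Each setting used 8,000 simulated trials with N = 200, four equal centres and permuted blocks of ten. Centre sizes and block length are assumptions. Type I error without centre was .047, .047 and .038 at shares of 2%, 5% and 10%; with centre it was .049, .052 and .050. Power without versus with centre was .804 vs .811, .801 vs .813 and .808 vs .833. The Monte Carlo standard error of a type I error near .05 is √(.05 × .95/8000) = .0024, so the simulation agrees with the formulas.

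**The case against.** The strongest reply is that a journal article condenses the plan. Its Data analyses section does not say that its list of adjustments is complete, and a separate analysis plan may add the stratification factor. That is fair as far as it goes: the article does not show that centre will be left out of the final analysis. But it does state a model, and that model, followed as written, omits the factor on which allocation was blocked.

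A second reply is that age, gender and education are themselves recorded at baseline, so the two sections could describe one model with baseline BMI-SDS plus those three. This is a possible reading, so it would go too far to say that the article commits to two rival primary models. It still names different sets in two places, and neither reading brings in centre.

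Three stronger inferences are tempting and are not supported:

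- **Inflated false positives or a wrong sample size.** The error is in the conservative direction, and N = 199 stands under every covariate set tried.
- **A power gain of about 1, 2 and 4 points from adding centre.** That measures the model with centre against .80. Power without centre also rises when allocation is blocked, so the like-for-like gain is about 0.5, 1.3 and 2.7 points.
- **A large loss because baseline BMI-SDS is absent from the sample-size model.** Data analyses already adjusts for baseline, so that precision is not forgone. The article also does not say whether f = .2 is meant before or after that adjustment.

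**Conclusion.** The point holds, at modest size. The design blocks on centre and the stated ANCOVA has no centre term. At assumed centre shares of 2% to 10%, standard errors are about 1% to 5.4% too wide, type I error is about .048 to .039 instead of .05, and 0.5 to 2.7 points of power are lost at N = 199 and f = .2. These figures rest wholly on the assumed shares and on arms balanced within centre. With no centre effect there is no loss. The treatment estimate itself is hardly affected.

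The covariate difference between the sample-size and analysis sections is a matter of specification, with no numerical consequence for N. It should be settled so that the covariate set is fixed before the data are seen.

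**What to change.** In Data analyses, add centre as a fixed effect with four levels to the primary and secondary ANCOVAs, alongside the baseline value of the outcome analysed. State one covariate set, and use the same set in Sample size and enrolment and in Data analyses, saying explicitly whether age, gender and educational background are included. Leave the definition of the outcome and its time points as it is; this point gives no reason to alter it.

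The cost is one or two sentences and three degrees of freedom. Centre is already known from the randomisation, no new data are needed, and the sample size stays at 199 analysed and 226 randomised.
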